### Data collection between May 2017 and August 2020

The two-stage screening will be conducted to find and recruit potential study participants. A trained fieldworker will first screen to assess eligibility for criteria 1–3 in pre-ART counselling sessions and in individuals from randomly selected households in the community. Eligible participants will then be referred to the QECH to complete screening for criteria 4–9, and if eligible consented to participate in the study. At study visits, a tablet-based, standardised Open Data Kit case report form will be administered in one-on-one interviews by a study nurse to capture demographic and clinical data. Study data will be collected as outlined in table 1. Daily upload of electronic data will occur with oversight from the data manager at MLW. We will collect up to 30 mL of whole blood. Urine albumin to Creatinine ratio (ACR) dipstick test will be used to test for creatinine, proteinuria and glucosuria. In a subset of participants, an ECG supported by a digital platform and echocardiogram will be performed at baseline and at 6 and 24 months, as well as in any participant experiencing a clinical event suggestive of a cardiac aetiology. To facilitate the retention and clinical referrals of participants, contact will be made every 3 months to assess the occurrence of clinical events. Participants who miss a scheduled study visit will be contacted by phone and/or visited at home to assess their willingness to maintain their participation and to record intervening clinical events. Recording and definitions of other clinical events, including HIV-associated events, will be evaluated by the ERC chair. SMS (short message service) messages will be used for appointment reminders. A technical appendix, statistical code and study data sets will be made available from a data repository, after publication of our work.

### Sample size and statistical analysis

The required sample size for the study’s primary objectives is 800 HIV-infected patients and 190 HIV-uninfected adults using standard, normal distribution approximation sample size formulas for comparing proportions in two groups of unequal size and based on the following assumptions: (1) of HIV-infected study participants, 18.4% have abnormal PWV at baseline. We will exclude these participants from analysis. The 18.4% figure is informed by our ongoing studies of vasculopathy in HIV-infected patients, where this is the percentage of participants aged ≥35 years who have a PWV (>12 m/s). (2) Of both HIV-infected patients and HIV-uninfected adults, 20% will be lost to follow-up, including by death and HIV seroconversion.^40 41^ (3) The minimum relative risk (RR) of interest is 2 for objective 1 and 1.8 for objective 2. (4) The 24-month cumulative risk of clinically significant vasculopathy over study follow-up is 18.4% in the HIV-positive group. This is based on the same study data cited in (1). (5) For objectives 2a–2c, the exposure prevalence for each risk factor is 20%. (6) Statistical tests will have 80% power based on a two-sided test with α=0.05. Testing of hypotheses for the secondary outcome will be exploratory. However, we estimate 26 strokes (4 mimics), an unknown number of MIs and 80 deaths occurring during the study.^7 42^ Taken together, assumptions (3), (4) and (5) mean that, for 80% power, we assume a 24-month cumulative vasculopathy risk of 9.2% in HIV-negative participants, 18.4% in all HIV-infected participants, 15.9% in HIV-infected participants not exposed to the risk factors from objectives 2a–2c and 28.6% in the HIV-infected participants exposed to these risk factors.

The reporting of this study will be prepared in accordance with the Strengthening the Reporting of Observational Studies in Epidemiology guidelines.^43^ Summary and descriptive statistics will be tabulated for all primary and secondary outcome variables, as well as for exposure variables and potential confounding or mediating factors. Time plots for all outcome variables will be inspected. Quantitative data analysis will be conducted to assess the primary outcomes.

There will be three analysis time points: (1) after recruitment has finished and baseline data are available for all participants (baseline analysis); (2) once every participant has completed 6 months in the study (6-month analysis); and (3) at 36 months, when each participant has completed 24 months in the study (final analysis).

The baseline analysis will largely consist of descriptive statistics on participant characteristics and data recorded at baseline. Simple regression models will also be used to investigate relationships between exposure and outcome variables measured at baseline. Unadjusted analyses will consist of paired t-tests or Wilcoxon signed-rank tests (depending on whether the data are normally distributed or not) for continuously measured variables, and χ^2^ or Fisher’s exact tests (depending on contingency table cell counts) for binary and categorical variables. Adjusted analyses will be conducted using generalised linear models (GLMs).

The 6-month analysis will be limited in scope and serves two purposes: (1) characterise new-onset vasculopathy in HIV-infected participants who have initiated ART treatment at baseline (vascular IRIS) and (2) define vasculopathy outcomes for the final analysis. The main analysis of the study data will be conducted at the final analysis time point.

For objective 1 we will develop three regression models. Two GLMs will be developed to compare mean progression of arterial damage from baseline in HIV-infected ART patients and HIV-uninfected adults. These models will regress change from baseline PWV and CIMT, respectively, on HIV status. We will develop a third model to estimate the RR and population-attributable fraction of new-onset arterial damage in HIV-infected patients compared with HIV-uninfected adults.

For objective 2a, a set of GLMs will be developed to compare mean progression of vasculopathy in HIV-infected ART patients with and without reactivated latent herpes viral infection. These models will regress PWV and CIMT, respectively, on, on two log-transformed variables for antibody titres of CMV and VZV.

For objective 2b, we will again fit a set of GLMs, with change from baseline in PWV as response variable, this time to investigate if, in HIV-infected ART patients, there is an association between progression of vasculopathy and immune activation and inflammation biomarkers (IL-6, Intracellular adehesion molecule [ICAM], CD163). Specifically, for each marker, we will regress PWV on marker quantiles. After having built models for each marker, we will then develop comprehensive multiple regression models for PWV and CIMT with multiple independent markers as predictor variables.

For objective 2c, we will proceed as for objective 2a, but comparing HIV-infected ART patients with incomplete virological suppression or virological resurgence of HIV with those with suppressed HIV plasma viral load.

In addition to these analyses, given the repeated measurements for PWV, immune activation and inflammation markers, we will extend the GLMs for PWV to linear mixed models taking full account of the longitudinal nature of the data. Mixed models will also handle deviations from the visit schedule in a principled fashion and use all available data for dropouts. If a log link function is required for PWV in the GLMs, we will fit marginalised models using Generlaised Estimating Equations [GEE] instead of Linear Mixed Models [LMMs].

For the secondary study objectives, we will use univariate methods to assess the frequency of clinical events within exposure strata. If there are sufficient numbers of clinical events, we will develop Poisson or negative binomial regression models (depending on model fit) for each clinical event type to compare exposure-defined participants.

We will also use time-to-event models, specifically Cox proportional hazard models, to investigate associations between all-cause mortality and exposures.

As part of exploratory analyses, we will aim to identify risk groups that are potentially incompletely captured with the measured exposure variables. We will perform unsupervised group-based multitrajectory modelling of multivariate longitudinal patient trajectories to confirm any associations we have found using more traditional approaches.^44^

All efforts will be made to collect complete data on all study participants. However, there will inevitably be missing data due to dropouts and a variety of other reasons. All primary analyses will be performed using multiple imputation. For sensitivity analyses, we will use all available cases, direct likelihood and fully Bayesian models, and for GEE models weighted GEE. If the number of missingness patterns is sufficiently small, we will also use pattern mixture models which can be used under the general missing-not-at-random setting but make additional identification assumptions.

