### Study participants

Study inclusion criteria will be (1) age ≥35 years and (2) resident of Blantyre. HIV-infected patients must further be (3) ART-naïve or initiated ART <10 days prior to enrolment and (4) initiating standard first-line ART. Adult controls must further be (5) HIV-uninfected. Study exclusion criteria are (6) clinical history of CBD/CVD, (7) pregnancy, (8) critical illness or symptomatic anaemia at baseline, and (9) enrolment in an intervention study. At the analysis stage abnormal pulse wave velocity (PWV) at baseline (as defined in table 2) will be excluded for new-onset vasculopathy analysis but not for progression of vasculopathy. The same approach will be applied for baseline carotid intima-media thickness (CIMT) measurements. If the study participant becomes pregnant after recruitment, they will be withdrawn.

**Table 2 T2:** Case definitions of primary and secondary endpoints for the study

Type	Definitions
Primary endpoint	Carotid intima-media thickness (CIMT)	*The occurrence of new-onset vasculopathy**(**CIMT, a measure of atherosclerosis**)*: CIMT >0.9 mm or >75th percentile of age/sex references values or presence of plaque on the carotid scan. *Progression*: total change in CIMT at 24 months from baseline.
	Pulse wave velocity (PWV)	*Occurrence of new-onset vasculopathy**(**PWV*,*a measure of arterial stiffness**)*: PWV >12 (m/s). *Progression*: total change in PWV at 24 months from baseline.
Secondary endpoint	Stroke	*Confirmed (**1**+**2**) or 3 or 4 or 5:* Acute onset with a clinically compatible course, including unequivocal objective findings of a localising neurological deficit. CT or MRI compatible with a diagnosis of stroke and current neurological signs and symptoms. Stroke diagnosed as the cause of death at autopsy. Clinical history and positive lumbar puncture compatible with subarachnoid haemorrhage. Death certificate or death note from medical record listing stroke as the cause of death.

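### Objective 1's stated 80% power removes baseline-abnormal PWV from the HIV-infected group only, while the new-onset analysis rule also removes controls

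*Protocol article*

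**What the plan says.** All references are to the protocol article.

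- Sample size and statistical analysis gives the target: "The required sample size for the study’s primary objectives is 800 HIV-infected patients and 190 HIV-uninfected adults". The method is described as "normal distribution approximation sample size formulas for comparing proportions in two groups of unequal size", and no variant is named.
- Assumption (1) in that section deducts abnormal baseline PWV from one group: "1) of HIV-infected study participants, 18.4% have abnormal PWV at baseline. We will exclude these participants from analysis".
- Assumption (2) deducts attrition from both: "Of both HIV-infected patients and HIV-uninfected adults, 20% will be lost to follow-up, including by death and HIV seroconversion".
- Assumption (3) sets the effect: "The minimum relative risk (RR) of interest is 2 for objective 1 and 1.8 for objective 2". The resulting 24-month risks for objective 1 are 9.2% (HIV-negative) and 18.4% (HIV-infected), with 80% power and two-sided α of 0.05.
- Study participants gives the analysis rule: "At the analysis stage abnormal pulse wave velocity (PWV) at baseline (as defined in table 2) will be excluded for new-onset vasculopathy analysis". The rule does not mention HIV status, and the same sentence keeps these participants in the progression analysis. It then adds: "The same approach will be applied for baseline carotid intima-media thickness (CIMT) measurements".
- Table 2 defines abnormal CIMT as "CIMT >0.9 mm or >75th percentile of age/sex references values or presence of plaque on the carotid scan".
- The third objective 1 model estimates the relative risk of new-onset arterial damage in HIV-infected against HIV-uninfected participants.

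**The concern.** The rule for the new-onset analysis applies to everyone, and it must: a control already above 12 m/s at baseline cannot develop new-onset stiffness. The power statement lists the deduction for one group only. Assumption (2) names both groups, so the wording of assumption (1) cannot easily be read as shorthand for both.

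Controls are the smaller group by more than three to one, so they limit the precision of the objective 1 comparison. If some of the 152 controls left after attrition are also removed for abnormal baseline PWV, the stated 80% rests on more evaluable controls than the analysis will have. What is at stake is the accuracy of a stated power figure. The validity of the analysis is not in question.

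**Working it through.** **Inputs (Sample size and statistical analysis).** 800 HIV-infected and 190 controls; 18.4% baseline exclusion stated for the HIV-infected; 20% loss in both groups; risks p1 = 0.184 and p2 = 0.092, so Δ = 0.092; two-sided α = 0.05, z = 1.96.

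**Evaluable numbers on the listed assumptions.**
- HIV-infected: n1 = 800 × 0.816 × 0.80 = 522.2
- Controls: n2 = 190 × 0.80 = 152

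**Reproducing the stated power, pooled-variance formula.** Power = Φ[(Δ − z·s0)/s1], where s0 = √[p̄(1−p̄)(1/n1 + 1/n2)] and s1 = √[p1(1−p1)/n1 + p2(1−p2)/n2].
- p̄ = (522.2 × 0.184 + 152 × 0.092)/674.2 = 0.1633
- s0 = 0.03406 and s1 = 0.02893
- (0.092 − 1.96 × 0.03406)/0.02893 = 0.872, so power = 80.8%

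Solving for 80% with n1 = 522 gives 149 evaluable controls, and 149/0.80 = 186, close to the stated 190. The margin is 152 − 149 = 3 controls, about 2% of the group.

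**Arcsine normal approximation.** Power = Φ[h/√(1/n1 + 1/n2) − z], where h = 2·asin√0.184 − 2·asin√0.092 = 0.2703. At 522 and 152 this gives 83.5%.

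**Applying the analysis rule to controls.** The control prevalence of abnormal PWV is not given, so three values are assumed. The middle one halves the HIV-infected figure, in line with the relative risk of 2. The last equals the HIV-infected figure.

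| Controls excluded at baseline (assumed) | Evaluable controls | Power, pooled | Power, arcsine | Detectable RR, 80% pooled power |
|---|---|---|---|---|
| 0% | 152 × 1.000 = 152 | 80.8% | 83.5% | 1.98 |
| 5% | 152 × 0.950 = 144 | 79.0% | 82.0% | 2.02 |
| 9.2% | 152 × 0.908 = 138 | 77.3% | 80.6% | 2.05 |
| 18.4% | 152 × 0.816 = 124 | 73.1% | 77.2% | 2.14 |

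The detectable RR holds the HIV-infected risk at 18.4% and lowers the control risk until pooled power reaches 80%.

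**Does the figure of 190 show which deduction was made?** No.
- Pooled, no control exclusion: 149/0.80 = 186.
- Arcsine, 9.2% control exclusion: 135.2 evaluable needed, and 135.2/(0.80 × 0.908) = 186.

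Objective 2 (28.6% against 15.9%, 20% exposed) does not identify the formula either. The pooled formula needs 492 evaluable, and 492/(0.816 × 0.80) = 754. The arcsine formula needs 516, which by the same division is 791. Both lie below 800, and the arcsine result is nearer.

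**The case against.** **The back-calculation proves nothing about the control group.** This stands. A reader might infer that 190 can be reached only if no control was removed at baseline. As shown above, the arcsine approximation reaches the same 186 with a 9.2% control exclusion, and the article names no variant. The point therefore rests on the wording of assumption (1) against the analysis rule.

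**The shortfall depends on a figure the article does not give.** This also stands. At 2% exclusion pooled power is still about 80%, and at 5% it is 79.0%, a difference of rounding. The 18.4% case assumes controls are as often abnormal as HIV-infected patients, which fits poorly with the study hypothesis. Under the arcsine formula power stays above 80% at 9.2%. A flat statement that 80% power is not delivered would go too far.

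**An unpooled formula stays above 80% throughout.** It gives 84.3% even at 124 controls. But with no control exclusion it would need only 106 evaluable controls (106/0.80 = 132 enrolled), and at 18.4% exclusion 106/(0.80 × 0.816) = 162. It does not explain 190.

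**A journal article condenses.** The full protocol may record a control deduction. But the article does list its assumptions, and it limits this one to a single group while its own analysis rule has no such limit. That is an inconsistency in what is stated.

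**CIMT.** A reader might go on to put a power figure on new-onset CIMT, taking a quarter of participants as abnormal under the percentile rule. The article does not support that. It does not identify the reference population and gives no CIMT incidence, and its risks come from PWV data.

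**Conclusion.** The inconsistency is real and modest in size. The power statement lists a baseline PWV exclusion for the HIV-infected only, while the new-onset analysis applies it to both groups. On the listed assumptions pooled power is 80.8%, and it falls below 80% once more than about 2% of controls are excluded. How far it falls depends on an assumed control prevalence: to between 79% and 73% (pooled), or between 82% and 77% (arcsine), for 5% to 18.4% excluded.

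The effect is confined to one of objective 1's three models, the binary new-onset comparison. The two progression models keep baseline-abnormal participants, and objective 2 uses no controls. For new-onset CIMT the article states no baseline exclusion in either group and no CIMT-specific risk, so the 80% should not be read as covering that endpoint.

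**What to change.** In Sample size and statistical analysis:

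1. Add to assumption (1) the baseline PWV exclusion assumed for HIV-uninfected adults, or state that none was assumed.
2. Name the formula variant that produced 800 and 190.
3. Restate objective 1 power for new-onset PWV, or the detectable relative risk, over a range of control exclusions. With the pooled formula this is about 79% to 73%, or a relative risk of about 2.02 to 2.14, for 5% to 18.4% excluded.
4. State that the 80% refers to new-onset PWV and was not derived for new-onset CIMT.

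The cost is a few sentences and, under the pooled formula, a slightly less favourable figure. Enrolment, conduct and the planned models do not change.

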### Study objectives

This study will test the hypothesis that immune activation and dysfunction, driven by HIV and reactivation of latent CMV/VZV herpesvirus infections, lead to increased CBD/CVD risk in adults aged ≥35 years in SSA. We will address this through the following objectives:

To determine if progression of the surrogate marker of CBD/CVD or occurrence of new-onset vasculopathy is higher in adults aged ≥35 years with HIV infection on ART compared with those without HIV.To determine if progression of surrogate markers of CBD/CVD or occurrence of new-onset vasculopathy is higher in adults aged ≥35 years with HIV/herpes viral antigenaemia or chronic immune activation compared with those without HIV/herpes viral antigenaemia or chronic immune activation. Specifically, we will determine if progression of surrogate markers or new-onset vasculopathy is higher in the following:In ART patients with reactivated latent herpes viral infection, compared with those without reactivated latent herpes viral infection.In ART patients with the highest 25% of markers for immune activation, inflammation or endothelial activation compared with the bottom 25%.In ART patients with incomplete virological suppression or virological resurgence of HIV, compared with those with suppressed HIV plasma viral load.

The secondary study objectives are to determine if viral antigenaemia or chronic immune activation increases the occurrence of the following clinical events: (1) stroke, (2) MI, (3) angina (excluding MI), (4) peripheral vascular disease (PVD), (5) all-cause death/vascular-related death and (6) immune reconstitution inflammatory vasculopathy.

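### The 80% power stated for objective 2 assumes a 20%/80% exposure split that does not describe objective 2b's top-versus-bottom-quartile contrast; at RR 1.8 the 2b new-onset comparison falls short of 80%

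*Protocol article*

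**What the plan says.** All statements are in the protocol article.

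- *Study objectives*, objective 2b: the contrast is "In ART patients with the highest 25% of markers for immune activation, inflammation or endothelial activation compared with the bottom 25" per cent. The outcomes named for objective 2 are progression of the surrogate markers or new-onset vasculopathy.
- *Sample size and statistical analysis*: "The required sample size for the study’s primary objectives is 800 HIV-infected patients and 190 HIV-uninfected adults", obtained with "standard, normal distribution approximation sample size formulas for comparing proportions in two groups of unequal size".
- Same section, effect size: "The minimum relative risk (RR) of interest is 2 for objective 1 and 1.8 for objective 2".
- Same section, exposure: "5) For objectives 2a–2c, the exposure prevalence for each risk factor is 20" per cent.
- Same section, power: "Statistical tests will have 80% power based on a two-sided test with α=0.05".
- Same section, losses: "of HIV-infected study participants, 18.4% have abnormal PWV at baseline. We will exclude these participants from analysis", and "20% will be lost to follow-up, including by death and HIV seroconversion".
- Same section, resulting risks for objectives 2a to 2c: 15.9% in unexposed and 28.6% in exposed HIV-infected participants, with 18.4% overall.

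No separate calculation is given for 2b. The analysis text for 2b in the same section plans to regress change in PWV on marker quantiles.

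**The concern.** The sample size statement names 2b among the objectives with 20% exposed and, by implication, 80% unexposed. Objective 2b has neither group. It has two equal quarters, and half of the ART patients contribute to neither side. The exposed group grows slightly, but the reference group shrinks from roughly 400 to roughly 130, which costs more precision than the larger exposed group gains.

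2b is a primary objective and carries the inflammation part of the study hypothesis. A reader who takes the 80% at face value would expect a true RR of 1.8 to be missed one time in five. If the chance of missing it is a third or more, a null new-onset result for IL-6, ICAM or CD163 could be read as stronger evidence of no association than it is.

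**Working it through.** **Inputs, all from the sample size section unless noted.** 800 HIV-infected patients; 18.4% excluded for abnormal baseline PWV; 20% lost; RR 1.8; overall 24-month risk 18.4%; two-sided alpha 0.05. The quartile contrast is from the study objectives.

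**Formula.** Normal approximation for two proportions, pooled variance under the null:
power = Φ[(p1 − p0 − 1.96·SE0) / SE1], where SE0 = √[p̄(1−p̄)(1/n1 + 1/n0)] and SE1 = √[p1(1−p1)/n1 + p0(1−p0)/n0].

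**Evaluable patients.** The article does not say how the two losses combine, so both ways are shown.
- Multiplicative: 800 × 0.816 × 0.80 = 522
- Additive: 800 × (1 − 0.184 − 0.20) = 493

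**Step 1: reproduce the plan's figure (20% v 80%).**
- Risks: 0.184 / (0.8 + 0.2 × 1.8) = 15.9%; × 1.8 = 28.6%. Both match the article.
- 522 evaluable, 104 v 418: (0.127 − 1.96 × 0.0424) / 0.0477 = 0.92, power 82.1%.
- 493 evaluable, 99 v 394: (0.127 − 1.96 × 0.0437) / 0.0491 = 0.84, power 80.0%.

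The plan's 80% is therefore correct for the split it assumes, and the same formula can be carried to 2b.

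**Step 2: top v bottom quartile at the stated risks (28.6% v 15.9%).**
- 522 evaluable, 522/4 ≈ 131 per group: (0.127 − 1.96 × 0.0515) / 0.0509 = 0.51, power 69.6%.
- 493 evaluable, 493/4 ≈ 123 per group: power 67.1%.

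This is a generous case. With those two quartile risks, an overall risk of 18.4% requires a middle-half risk of (0.184 − 0.25 × 0.286 − 0.25 × 0.159) / 0.5 = 14.55%, which is below the bottom quartile. If the middle half is no lower than the bottom quartile, the overall risk is at least 0.25 × 28.6 + 0.75 × 15.9 = 19.1%, not 18.4%.

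**Step 3: hold the overall risk at 18.4%, RR 1.8 top v bottom.** The document gives no middle-half risk, so it is an assumption here. Let m be the middle half's RR against the bottom quartile. Then the bottom-quartile risk is 0.184 / (0.25 + 0.5m + 0.25 × 1.8).

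| Middle half assumed | Bottom v top risk | Power, 131 per group | Power, 123 per group |
|---|---|---|---|
| As bottom quartile (m = 1) | 15.3% v 27.6% | 67.7% | 65.1% |
| Intermediate (m = 1.4) | 13.1% v 23.7% | 59.3% | 56.8% |
| As top quartile (m = 1.8) | 11.5% v 20.7% | 52.5% | 50.2% |

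**Step 4: detectable RR.** With 131 per group and the bottom-quartile risk fixed, 80% power needs an RR of about 1.92 at a risk of 15.9%, or about 2.06 at 13.1%.

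**Step 5: source of the loss.** Top 25% against the remaining 75% would have about 84 to 87% power. The shortfall comes from dropping the middle half, not from using 25% in place of 20%.

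**The case against.** The strongest reply is that RR 1.8 was derived for exposed against all unexposed patients, and that the extremes of a marker should differ by more than that. If 1.8 is read as top quartile against the rest, with the overall risk at 18.4% and a log-linear gradient across quartiles, the top-v-bottom RR is about 2.53 (27.6% v 10.9%). The same 131 v 131 contrast then has about 93% power (92% with 123 per group). This arithmetic stands, and it shows that any shortfall is conditional on what 1.8 refers to. It is the less natural reading, because the article sets 1.8 as the minimum RR of interest for objective 2 without distinction and defines 2b as top against bottom.

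A second reply is that the planned 2b model regresses change in PWV on marker quantiles. That outcome is continuous, nothing says the middle quantiles are dropped, and under *Study participants* abnormal baseline PWV is not an exclusion for progression. This also stands. No standard deviation or mean difference is given, so that model's power cannot be derived in either direction. It therefore cannot support the stated 80%, which is claimed from a comparison of proportions, and new-onset vasculopathy is one of the outcomes named for 2b.

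A reader might infer that objective 2b as a whole has only about 59 to 70% power. The documents do not support that. The upper figure sits awkwardly with the stated overall risk, the lower one needs a middle-half risk that the article does not give, and both concern the binary endpoint only. Nor should a reader infer that the sample size arithmetic is wrong: it reproduces for the split it assumes.

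**Conclusion.** The point holds in a limited form. The 20% exposure assumption does not describe objective 2b, and the 80% power does not hold for 2b's new-onset comparison at RR 1.8 between top and bottom quartiles. Under that reading power is at most about 67 to 70%, and about 50 to 68% with the overall risk held at 18.4% (about 57 to 59% if the middle half is intermediate). All these figures lie below 80%. That conclusion does not depend on how losses combine or on the middle-half assumption, but the exact figure does. It does depend on taking 1.8 as the top-v-bottom RR.

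This should be fixed because it concerns the stated power of a primary objective. It does not affect recruitment, data collection or the planned models.

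**What to change.** 1. In the sample size section, restrict the 20% exposure assumption to objectives 2a and 2c.
2. For 2b, state that RR 1.8 refers to top against bottom quartile. Then give either its power (below 80%, with the middle-half assumption shown) or its detectable RR for 80% power (about 1.9 to 2.1).
3. Say that these figures apply to the binary new-onset endpoint and not to the regression of PWV change on marker quantiles.
4. If RR 1.8 was intended for the top quartile against all other ART patients, redefine 2b that way in the study objectives instead.

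The cost is rewording, plus a less favourable power statement for 2b unless item 4 applies. No extra patients are required.

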**Methods and analysis:**

We will conduct a single-centre, 36-month, prospective cohort study in 800 HIV-infected patients initiating ART and 190 HIV-uninfected controls in Blantyre, Malawi. Patients and controls will be recruited from government ART clinics and the community, respectively, and will be frequency-matched by 5-year age band and sex. At baseline and follow-up visits, we will measure carotid intima-media thickness and pulse wave velocity as surrogate markers of vasculopathy, and will be used to estimate CBD/CVD risk. Our primary exposures of interest are cytomegalovirus and varicella zoster reactivation, changes in HIV plasma viral load, and markers of systemic inflammation and endothelial function. Multivariable regression models will be developed to assess the study’s primary hypothesis. The occurrence of clinical CBD/CVD will be assessed as secondary study endpoints.

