## Methods and analysis

### Study design

To address objective 1, we will conduct a single-centre, 36-month, prospective cohort study in 800 HIV-infected patients initiating ART and 190 HIV-uninfected adults aged ≥35 years. HIV-infected and HIV-uninfected participants will be frequency-matched by 5-year age band and sex. On a 6-monthly basis, we will measure markers of viral infection, inflammation and endothelial function along with surrogate markers for CBD/CVD (table 1).

**Table 1 T1:** Laboratory tests and clinical procedures in ART patients and HIV-uninfected adults

	Study time points						
	Baseline	6 months	12 months	18 months	24 months	30 months	36 months
Clinical procedures							
PWV	X	X	X	X	X	X	X
CIMT	X				X		
ABPI	X	X	X	X	X	X	X
Cardiac echo (participant subset)	X				X		
ECG (participant subset)	X				X		
Cardiometabolic markers							
Creatinine Full blood count	X X	X			X		
Cholesterol (LDL, HDL, triglycerides)	X				X		
Serum glucose/haemoglobin A1c	X				X		
HIV infection and progression							
HIV viral load (patients with HIV)	X	X	X				
CD4 count (patients with HIV)	X	X	X				
HIV rapid test (controls)	X		X		X		X
Immune dysregulation							
Soluble markers of systemic inflammation	X	X	X				
Soluble markers of endothelial activation	X	X	X				
CD8 and CD4 T cell activation and senescence (participant subset)	X	X	X		X		X
Monocyte/Macrophage activation and senescence (participant subset)	X	X	X		X		X
Herpesviruses infection							
CMV IgG	X	X					
VZV IgG	X	X					

ABPI, Ankle Brachial Pressure Index; ART, antiretroviral therapy; CIMT, carotid intima-media thickness; CMV, cytomegalovirus; HDL, high-density lipoprotein; LDL, low-density lipoprotein; PWV, pulse wave velocity; VZV, varicella zoster virus.

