### Exposures

The exposure for primary objective 1 will be HIV status. Yearly HIV rapid tests in HIV-uninfected adults will be performed to exclude those with new HIV infections (figure 2).

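### The unadjusted baseline analysis names paired tests, but at baseline the design contains no pairs; unpaired tests are needed (low to moderate severity, confined to that analysis)

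*Protocol article*

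**What the plan says.** All references are to the protocol article.

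- **Sample size and statistical analysis, baseline analysis paragraph.** The analysis is mainly descriptive. Simple regression models are added to "investigate relationships between exposure and outcome variables measured at baseline". For continuous variables the next sentence reads: "Unadjusted analyses will consist of paired t-tests or Wilcoxon signed-rank tests", with the choice between the two depending on normality. For binary and categorical variables it names chi-square or Fisher's exact tests. Adjusted analyses use generalised linear models (GLMs).
- **Study design.** "HIV-infected and HIV-uninfected participants will be frequency-matched by 5-year age band and sex".
- **Abstract, Methods and analysis.** "Patients and controls will be recruited from government ART clinics and the community, respectively". Study setting adds pre-ART counselling sessions as a source of controls, but describes no linking of a control to a patient.
- **Sample size and statistical analysis, first paragraph.** The study needs "800 HIV-infected patients and 190 HIV-uninfected adults", from formulas "for comparing proportions in two groups of unequal size".
- **Exposures.** "The exposure for primary objective 1 will be HIV status". Under Study objectives, the contrasts for objective 2 are also between different people: reactivated herpesvirus infection or not, top or bottom quarter of a marker, HIV viral load suppressed or not.

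**The concern.** A paired t-test or signed-rank test works on differences within linked pairs, either two measurements on one person or two individually matched people. The baseline analysis has neither. Frequency matching makes the age and sex distributions of the two groups similar, but does not attach a given control to a given patient. The same holds within the HIV-infected group, where exposed and unexposed patients are unlinked.

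An analyst who followed the text would either be unable to run the test or would have to invent a pairing. Invented pairs would leave most patients out and make the P-value depend on which pairs were chosen. An analyst who quietly used the unpaired test would get the right analysis, but as an undocumented departure from the published plan.

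**Working it through.** **1. Which design do the protocol's own numbers assume?**

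Inputs, all from Sample size and statistical analysis: 800 and 190 recruited; 18.4% of patients excluded for abnormal baseline pulse wave velocity; 20% lost in both groups; 24-month risks of 18.4% and 9.2%; two-sided α = 0.05; 80% power.

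- Evaluable patients: 800 × 0.816 × 0.8 = 522
- Evaluable controls: 190 × 0.8 = 152
- Pooled risk: (152 × 0.092 + 522 × 0.184) / 674 = 0.163
- SE under the null: √[0.163 × 0.837 × (1/152 + 1/522)] = 0.0341
- SE under the alternative: √[0.092 × 0.908/152 + 0.184 × 0.816/522] = 0.0289
- Power: Φ[(0.092 − 1.96 × 0.0341) / 0.0289] = Φ(0.87) ≈ 80.8%

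With 522 patients fixed, 149 evaluable controls suffice for 80% power, and 149 / 0.8 = 186.25, so 187 recruited against the stated 190. The stated size is reproduced by an ordinary comparison of two independent groups. No pairing enters it.

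**2. Could pairs arise anywhere at baseline?**

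| Possible source of pairs | What the protocol gives |
|---|---|
| Same person, two times | One time point in the baseline analysis |
| Individually matched people | Frequency matching by age band and sex only |
| Equal groups | 800 and 190, about 4.2 to 1 |
| Within-person exposure contrast | None; all contrasts are between persons |

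The paragraph does not name the groups to be compared. That does not rescue the wording, because no exposure contrast in the document is paired.

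**3. Is the paragraph consistent with itself?**

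Chi-square and Fisher's exact tests assume independent observations; paired binary data would call for McNemar's test. The simple regressions proposed just before also treat participants as independent: with a two-level exposure, such a regression is the equal-variance two-sample t-test. One paragraph thus treats the same people as independent twice and as paired once.

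**4. What would forced pairing cost?**

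This is hypothetical. Assume equal standard deviations (SD) in the two groups and write ρ for the within-pair correlation.

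- Most pairs possible: 190. Unused patients: 800 − 190 = 610, or 610/800 = 76%
- Unpaired SE, all 990 people: √(1/800 + 1/190) = 0.081 SD
- Paired SE, 190 pairs: √[2(1 − ρ)/190]; at ρ = 0 this is 0.103 SD
- Ratio at ρ = 0: 0.1026 / 0.0807 = 1.27 (variance ratio 1.62)
- Difference detectable at 80% power, (1.960 + 0.842) × SE: 0.226 SD unpaired, 0.287 SD paired at ρ = 0
- Equal SEs when 2(1 − ρ)/190 = 1/800 + 1/190, which gives ρ = 0.38

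The penalty in SE therefore runs from 27% at ρ = 0 to none at ρ of about 0.38.

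**The case against.** The strongest reply is that little depends on this sentence. The baseline analysis is largely descriptive, and the main analysis is assigned to the final time point. Objectives 1 and 2 are addressed there by GLMs, extended to mixed models for pulse wave velocity, with a separate relative-risk model for new-onset damage. Even at baseline, the simple regressions and adjusted GLMs cover the same relationships with methods that suit unlinked groups. All of this stands, and it limits the severity.

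A second reply is that nobody would form the pairs. The independent-sample tests in the same sentence suggest a slip in naming, and an analyst would probably substitute the unpaired test. This also stands. A reader might infer from the group sizes that the plan discards 76% of its patients, or loses 27% in precision. The protocol does not support that, because it nowhere proposes to form pairs. Anyone who did pair would also probably do so within age band and sex, where some positive correlation is possible and the loss would be smaller.

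A third reply is that paired tests have a place in this study. They do: Table 1 schedules pulse wave velocity at seven visits and carotid intima-media thickness at two, so within-person change could be tested that way. But the sentence sits in the baseline paragraph, and a within-person test would not compare exposure groups.

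Nor is this a detail left to an analysis plan. The protocol names specific tests, and they do not fit its design.

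**Conclusion.** The statement is wrong as written, at low to moderate severity. Paired t-tests and signed-rank tests cannot validly be applied to the baseline comparisons, because the protocol creates no within-person or individually matched pairs at that time point. This conclusion rests on the text alone and does not depend on which exposure contrast is meant.

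The error is confined to the unadjusted baseline analysis of continuous variables. A reader might go further and conclude that the primary results or the power are compromised. They are not: the stated sample size already assumes independent groups, and neither the regression models at baseline nor the final models use these tests. The 27% increase in standard error applies only to an arbitrary 1:1 pairing with equal SDs and zero correlation, so it should be read as an illustration and not as an expected loss.

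**What to change.** In the baseline analysis paragraph, replace the two paired tests with unpaired two-sample t-tests or Wilcoxon rank-sum (Mann-Whitney) tests. Welch's version is a sensible choice with such unequal groups, but the essential change is from paired to unpaired. If the authors also want tests of within-person change between visits, state that separately, label it as such, and reserve the paired tests for it.

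The cost is a one-line wording change. Sample size, data collection, adjusted models and final analysis stay as they are.
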